### 2.7. Interventions

The control group will not receive any intervention but may receive orientations about sexuality by healthcare professionals such as social workers, nurses, psychologists, or physicians (oncologists, mastologists, or gynecologists), eventually considering that none of the institutions where the study will be undertaken has specific protocols or routines aimed at sexual and reproductive health.

Three telenursing counseling sessions will be carried out over 6 weeks in the intervention group. This period was chosen for being considerate enough to address the issues planned and to establish a bond and a relationship of trust between the researchers and the participants. Most educational interventions aimed at the sexual functioning of women with breast cancer are carried out in a period of 3 to 24 weeks.^[8,16,19,20]^ The sessions will take place at intervals of at least 15 days, considered enough for contacting all participants but not so long that would cause forgetfulness of the information provided in each contact.^[21]^

The calls will be made at times and days arranged with the participants and the researcher and are estimated to last 30 to 40 minutes. The telephone counseling will be conducted exclusively by the principal researcher to minimize the risks of divergence in the approach. The principal researcher has worked as a nurse practitioner in the public health system for approximately seven years, has a specialization degree in public health, has a master’s degree in nursing, and has worked with sexual dysfunction in women with breast cancer for 4 years.

The content of the counseling sessions will be based on the guidelines provided by the American Cancer Society for managing female sexual problems related to cancer. The contents were organized into 3 main topics: Cancer, sex, and the female body; How can treatments interfere with sexual life? And: managing female sexual problems related to cancer.^[22]^ The counseling sessions will be based on the constructs of social-cognitive theory.

Telenursing uses technologies to provide nursing care and direct nursing practice.^[23]^ Moreover, since 2008, the International Council of Nurses has considered telenursing a service that provides nurses with the administration of care to patients living in rural or remote areas and enables them to maintain effective communication with clients who have noncommunicable chronic diseases, providing an effective strategy to promote self-care and a healthy lifestyle.^[22]^ The telephone intervention eliminates visual contact, providing anonymity during the interactions. Furthermore, telephone calls enable greater inclusion of patients who live in rural areas or locations that are difficult to reach and who are often not prone to in-person interventions. Finally, telephone calls are considered an economical intervention method.^[24]^

### 2.8. Relevant concomitant care permitted or prohibited during the trial

Concomitant treatments for sexual dysfunction or menopausal symptoms will not be allowed during participation in the study since the comparison between the control and intervention groups does not allow cointerventions (medications, therapies, or behaviors) to avoid interferences regarding the outcome.^[14]^

### 2.9. Outcome

The study’s primary outcome will be sexual functioning, which will be assessed using the FSFI. The FSFI is an instrument built and validated in English^[18]^ and currently has at least 20 translations in different languages. The initial validation of the FSFI obtained a Cronbach’s alpha > 0.90 and reliability coefficient in the high general retest for all domains that make up the scale (*R* = 0.79 to 0.86), demonstrating good construct validity with a statistically significant difference between the averages of groups with and without sexual desire disorder (*P* < .001). The data above support the psychometric reliability and validity of the FSFI. In 2007, the FSFI was translated and validated into Portuguese (Brazil),^[25]^ obtaining a Cronbach’s alpha of 0.92 (95% CI: 0.90–0.93) and showing adequate internal consistency. The FSFI is a self-report questionnaire composed of 19 questions to evaluate female sexual functioning, which uses a Likert scale ranging from 0 to 5 and has 6 domains: desire, subjective arousal, lubrication, orgasm, satisfaction and pain (dyspareunia).^[26,27]^

Sexual function will be analyzed at baseline (*T*0), 6 weeks after the intervention (*T*1), and 12 weeks after the intervention (*T*2). In other studies that performed an intervention to improve the sexual functioning of women with breast cancer, the outcome was evaluated between 4 weeks and 12 months after the intervention.^[8,11]^

### 2.10. Blinding

Due to the nature of the intervention, it is impossible to blind the participants and the researcher responsible for providing and monitoring the intervention. Therefore, only research assistants who will evaluate the outcome after the intervention and the statistician who will perform the data analysis will be blinded concerning the participants’ group allocation.^[14]^

### 2.11. Strategies to improve adherence to interventions

Short Message Notifications will be sent to remember the subjects of the date and time of the scheduled sessions as a strategy to increase participants’ adherence to the study. Adherence will be assessed by participation in the telephone counseling sessions, which will be recorded in a specific form, including information such as the date and time of the intervention, duration, the topic addressed, and other relevant notes. In addition, a postintervention evaluation will include questions about the frequency, duration, and content offered through the counseling sessions.

### 2.12. Provisions for posttrial care

Adverse events will be evaluated by the number of participants who report possible worsening symptoms in the primary endpoint. In addition, participants will indicate whether they have experienced worsening symptoms of any kind in the postintervention survey.

### 2.13. Statistical methods

The data will be compiled and analyzed in the JASP program (Copyright 2013–2021 University of Amsterdam) Version JASP 0.15.^[27]^

Descriptive statistics will be obtained for the independent variables (means for continuous variables, absolute and relative frequencies for categorical variables, and their respective confidence intervals). An ANOVA statistical test for repeated measures will be completed to assess the extent to which the control and intervention groups differ concerning the outcome variable (sexual functioning) in the periods analyzed (*T*0, *T*1, and *T*2). All statistical analyses will be performed in collaboration with external statisticians, who will not be informed about the allocation of the groups.

The dataset generated or analyzed during this study will not be publicly available due to the ethics review act. However, it will be available from the corresponding author upon reasonable request and under the Brazilian guidelines for research collaboration and data transfer.

The study results will be submitted for publication in a peer-reviewed nursing journal. No professional writer will be involved.

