### 2.4. Sample size

G*power software, Version 3.1.9.6 (German University Heinrich-Heine Universitaet, Duesseldorf)^[15]^, was used to calculate the sample size by selecting “Test F” as the family of the test, considering that the analysis of variance (ANOVA) of repeated measures with intra- and intergroup interaction will be used to verify the null hypothesis.

The sample size estimation was made using an equation based on ANOVA, which took into account an effect of 0.085 (representing an effect size of at least 0.30 in the groups) and a power of 80% in the repeated measures design (2 groups, alpha = 0.05, nonsphericity correction = 0.5). Given the parameters above, the G*power software suggested 45 participants in each group (90 participants in total). Taking into account possible sample losses, a percentage of 20% was added, which totaled a sample of 108 participants.

This effect size was stipulated by a previous study, which identified an intermediate effect size (approximately 30%) for sexual functioning among the groups (control and intervention).^[16]^ The sphericity corresponds to one of the assumptions the data must meet so that ANOVA can be used, ranging from 0.5 to 1, with 0.5 being the most rigorous.^[15]^

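### The primary test makes pre-randomisation FSFI an outcome level and relies on a 2-df group-by-time interaction; it is valid and sized for, but a pre-named baseline-adjusted group difference would be more efficient and easier to interpret

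*Protocol article*

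**What the plan says.** - Protocol article, section 2.13: the ANOVA is to "assess the extent to which the control and intervention groups differ concerning the outcome variable (sexual functioning) in the periods analyzed", which the same sentence lists as T0, T1 and T2. All three assessments are levels of the outcome, and no baseline covariate is named.
- Section 2.4: "the analysis of variance (ANOVA) of repeated measures with intra- and intergroup interaction will be used to verify the null hypothesis". With two groups and three times this interaction has 2 numerator degrees of freedom before any sphericity correction.
- Section 2.4, sizing: the calculation "took into account an effect of 0.085 (representing an effect size of at least 0.30 in the groups"), with "a power of 80% in the repeated measures design" and the settings "2 groups, alpha = 0.05, nonsphericity correction = 0.5". The result is that "the G*power software suggested 45 participants in each group (90 participants in total"), raised to 108 for losses.
- Section 2.6 places randomisation after the baseline evaluations. Section 2.9 sets T0, T1 and T2 and does not single out either follow-up as primary.

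**The concern.** Because T0 precedes randomisation, the arms can differ there only by chance. Its value lies in explaining variation between women at T1 and T2, which is what a covariate does. As an outcome level in an interaction test, it is in effect subtracted in full, whatever its correlation with follow-up. That is less precise than adjustment unless the correlation is close to 1.

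The form of the test adds a second problem. The aim stated in the Introduction is to test the effect of counselling. A 2-df F statistic can be significant because of a gain, a loss, or a difference between T1 and T2. On its own it does not say which, and it carries no estimate or confidence interval.

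At stake are power at a fixed sample size and a primary result that can be read as a treatment effect. Power matters here because the Discussion (section 4) itself calls inclusion and retention uncertain.

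**Working it through.** **1. The plan's own figure.** Read 0.085 as partial eta-squared: f² = 0.085/0.915 = 0.0929, so f = 0.305, which matches the stated 0.30. With 2 groups, 3 measurements and epsilon 0.5:
- df1 = (2−1)(3−1)(0.5) = 1
- df2 = (90−2)(3−1)(0.5) = 88
- lambda = 0.0929 × 88 × 2 × 0.5 = 8.17

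Power is 80.7% at N = 90 and 79.8% at N = 88. The 90 is therefore reproduced, for the interaction test.

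**2. Inputs for the comparison.** From section 2.4: n = 45 per arm and alpha 0.05. Assumptions: SD 1, equal correlation rho among T0, T1 and T2, and an effect of d = 0.5 SD. The article gives no correlation for this analysis, so rho is varied from 0.4 to 0.7. Its only related figure is the retest coefficient of 0.79 to 0.86 in section 2.9, at best an upper guide.

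**3. Formulas (noncentral F).** With n/2 = 22.5:
- Interaction, 2 and 176 df: lambda = 22.5 × Σ(centred group differences)²/(1−rho)
- Adjusted T1/T2 mean, 1 and 87 df: lambda = 22.5 × (mean effect)²/[(1+rho)/2 − rho²]
- Adjusted single time, 1 and 87 df: lambda = 22.5 × d²/(1−rho²)
- Joint adjusted test of T1 and T2, 2 and 86 df: lambda = 22.5 × δ′Σ⁻¹δ, where Σ has diagonal 1−rho² and off-diagonal rho−rho²

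**4. Sustained effect, rho = 0.5.** The group differences are (0, 0.5, 0.5); centred, (−1/3, 1/6, 1/6), with sum of squares 1/6.
- Interaction: 22.5 × (1/6)/0.5 = 7.50, power 68%
- Adjusted mean: 22.5 × 0.25/0.50 = 11.25, power 91%
- Adjusted single time: 22.5 × 0.25/0.75 = 7.50, power 77%
- Joint adjusted: 11.25 on 2 df, power 85%

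Power over the range of rho:

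| Test | 0.4 | 0.5 | 0.6 | 0.7 |
|---|---|---|---|---|
| Interaction (plan) | 60% | 68% | 78% | 89% |
| Adjusted T1/T2 mean | 89% | 91% | 94% | 97% |
| Adjusted single time | 73% | 77% | 83% | 91% |
| Joint adjusted | 82% | 85% | 89% | 95% |

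At rho 0.8 the interaction and the adjusted single time both reach 97 to 98%, so one time point gains nothing there.

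**5. Simulation check.** In 20,000 simulated trials at rho 0.5, with d = 0.572 (which gives the interaction 80% power), the interaction had 80.1%, the adjusted mean 96.5% and the adjusted T2 87.2%. The formulas give 80.0%, 96.6% and 87.2%.

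**6. Effect at one follow-up only, d = 0.5, rho = 0.5.**
- Interaction: lambda 7.50, power 68%
- Adjusted mean: 22.5 × 0.0625/0.50 = 2.81, power 38%
- Adjusted test at the time of the effect: 77% (at the other time, only the 5% error rate)
- Joint adjusted: lambda 8.44, power 73%

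**7. At the plan's own effect, under sphericity.** lambda = 0.0929 × 88 × 2 = 16.35, which gives the interaction 95.7% at N = 90. For a sustained effect this is d = √(16.35(1−rho)/15), or 0.87, 0.74 and 0.57 SD at rho 0.3, 0.5 and 0.7. The assumed 0.5 SD is thus smaller than the plan's effect throughout the table. At most about 4 points can be gained at that effect.

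**The case against.** The strongest defence is that sections 2.4 and 2.13 are consistent with each other. The test that sizes the trial is the test to be run, its error rate is controlled when sphericity is handled, and the sizing used the lowest possible epsilon for three measurements. All of this stands.

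Four stronger readings are tempting, and the article does not support them:
- **That the trial is underpowered.** A reader might infer this from the 60 to 89% row. That row rests on an assumed effect below the plan's own; at the stated effect the interaction is adequately powered.
- **That the loss of power is large whatever happens.** It depends on the correlation, which is not given, on the pattern of effect and on the contrast chosen.
- **That the test is the group main effect, diluted by T0.** The sentence in section 2.13 alone could be read so, but section 2.4 says that ANOVA of "repeated measures with intra- and intergroup interaction will be used to verify the null hypothesis".
- **That the treatment effect cannot be estimated.** This is true of the omnibus F. Differences in change from T0 from the same model would be unbiased, though less precise: at rho 0.5 and 0.5 SD, 80% power at one time needs 128 women by change and 98 by adjustment. Such contrasts may be specified in an analysis plan that is not shown.

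What remains is that the article does fix the confirmatory test, and a better one is available from data already collected.

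**Conclusion.** The point holds as one of efficiency and interpretability, not of validity or a missed power target. For a sustained 0.5 SD effect and rho from 0.4 to 0.7, adjustment for T0 gains 8 to 29 points if T1 and T2 are averaged (97−89 and 89−60) and 2 to 13 points at a single time (91−89 and 73−60). These figures assume equal correlations, sphericity and complete data on 90 women. The ranking is not universal: averaging is the worse choice if the benefit appears at only one follow-up, whereas the adjusted test at that time or the joint adjusted test is not.

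**What to change.** In section 2.13, model total FSFI at T1 and T2 only, with group, time, group-by-time, T0 FSFI and T0-by-time. Name one baseline-adjusted group difference, with its 95% CI, as the confirmatory test. Use one named time point, or the T1/T2 mean if a sustained effect is expected, and give the reason. Report the other time point as secondary. If the sponsor cannot commit to a pattern of effect, the joint adjusted test of T1 and T2 is a safer omnibus choice than the present interaction, but the adjusted differences must then be reported beside it. Align the sentence in section 2.4 that names the test, and state the correlation assumed in any recalculation.

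The cost is wording: no new data and no additional women. The real price is that the contrast must be chosen before outcome data are seen by arm, and a wrong choice loses power, as step 6 of the working shows.

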### 2.14. Ethics approval and consent to participate

Ethical approval was obtained by the Research Ethics Committee of the Federal University of Ceará, Brazil, under opinion no. 461609 and CAAE no. 43072721.9.0000.5054; and the Maternity School Assis Chateaubriand, Ceará, Brazil, with opinion number 4742687 and certificate of ethical appreciation number 43072721.9.3002.5050.

Written informed consent will be obtained from all participants. All participants will receive a unique code number. The code will be stored separately from the survey data and will only be accessible to members of the research team. All data will be stored and processed under Brazilian law no. 13.709/2018 on data protection.^[29]^ The (Brazilian Clinical Trials Registry in Portuguese) will be notified of any changes in the trial registry if important changes regarding the conduction or protocol of the RCT are needed.

## 3. Results

Differences in levels of sexual function among women allocated to the control and intervention groups in the analyzed periods (*T*0, *T*1 and *T*2). In addition, there were differences in the scores of the domains of sexual function (desire, excitement, orgasm, satisfaction and pain).

## 4. Discussion

Some studies have already been developed using telehealth as a tool to apply educational interventions for breast cancer patients. However, different outcome variables have been studied, such as psychological suffering and coping,^[30]^ depression, fatigue, quality of life,^[24]^ and chemotherapy-related symptoms.^[31]^ A telephone counseling program assessed the improvement in psychosocial outcomes posttreatment of women with breast cancer to improve sexual health through variables such as anguish, depression, sexual dysfunction, and personal growth.^[10]^ Another study used a couple-based telephone intervention to address sexual issues.^[8]^ Furthermore, researchers have developed a multimodal nursing care program based on WeChat, consisting of chat software for the early rehabilitation of women after breast cancer surgery.^[32]^ However, none of these studies have specifically evaluated telenursing. The current study protocol describes the procedures for the clinical trial of telephone counseling.

Information and communication technologies and follow-up and monitoring systems, with an emphasis on telenursing, improve the health and self-care outcomes of people with one or more Chronic Noncommunicable Diseases. In addition, telenursing is considered a resource to improve the quality of life of these patients and reduce hospitalizations and costs. This tool has been used to educate patients and health professionals.^[33,34]^

The clinical trial design has several significant strengths. The first is that the RCT is considered the gold standard of clinical research, allowing more reliable conclusions regarding the effectiveness of interventions. In addition, the study has 2 parallel arms for comparing the intervention to usual care and will include a follow-up assessment of the outcome 12 weeks after the intervention in addition to the measurement that will take place immediately after the end of the intervention (6 weeks). Finally, the quality of the research data will possibly be high due to the use of validated instruments (such as the FSFI) for measuring sexual function. Regarding the weaknesses of the study, we can mention the nonmeasurement of the prevalence rate of sexual problems in the population and the uncertainty regarding the inclusion and retention rate, which can impact the time needed to achieve the sample size required for adequate statistical significance. Another limitation is the use of a nonactive treatment in the control group, which can generate a risk of general and nonspecific effects.

## 5. Conclusion

This evidence-based nursing care strategy can be used to improve the sexual function of breast cancer patients and consequently their quality of life and marital relationship.
